| 1. **Objectives, Specific Aims and Rationale**   *Objective*  To investigate the use of antibiotics and their protective effect against complications of infection to inform the development of risk prediction models to guide antibiotic treatment decisions for suspected infection in primary care.  *Aims*   1. Estimate the incidence of i) GP consultations for infection and ii) antibiotic prescriptions by: age-group, gender, SES, ethnicity, selected co-morbidities, obesity and smoking status 2. Describe antibiotic prescribing patterns linked to the reason for the prescription by: age-group, gender, SES, ethnicity, selected co-morbidities, obesity and smoking status 3. Estimate the incidence of adverse outcomes in the following 28 days including: hospital admission for infection; A&E admission; re-consultation for infection; re-consultation for antibiotic side-effects (rash, nausea, …) and death for patients with a GP consultation for i) respiratory tract infection ii) urinary tract iii) skin/soft tissue infection, comparing patients with each listed age/co-morbidity group (including smoking status and obesity) to non-comorbid patients 4. Estimate the number of patients needed to treat with antibiotics to avoid one infection-related adverse outcome, comparing the results for each age/co-morbidity group to non-comorbid patients 5. Develop risk prediction tools to support clinical decision making and communication with patients   *Rational*  We have previously shown that more than half of all antibiotic prescriptions in primary care are issued to less than 10% of patients, and that this 10% of patients have high levels of co-morbidity.1 Targeting such high-frequency users of antibiotics in antimicrobial stewardship programmes might provide opportunities for a more effective intervention approach. Underlying this hypothesis is the assumption that it might be safe and feasible to reduce prescribing in patients with the highest levels of antibiotic prescribing, many of whom have co-morbidity.  To investigate whether higher rates of antibiotic use are likely to be justified in higher risk patients compared to patients who lack these risk factors, we will undertake a series of studies to investigate which patients in terms of age, gender, SES, ethnicity, selected co-morbidities, obesity and smoking get the most antibiotics. We will determine which patients are most likely to receive antibiotics for which infections and relate this to national guidance on antibiotic prescribing. To estimate whether the protective effect of antibiotics differs according to the patient’s age and the presence of co-morbidity, obesity or their smoking status, we will estimate the risk of infection related adverse-outcomes, comparing patients who have been treated with antibiotics to those who have not been treated with antibiotics for each of these groups. We will use these estimates to calculate the number of patients who need to be treated with antibiotics to avoid one infection-related adverse outcome (NNT), accounting for age, gender, SES, ethnicity, co-morbidity, obesity and smoking status. This will inform the development and validation of individualised risk-prediction models to support clinical decision-making and patient communication around the need for antibiotic treatment for suspected infection in primary care. |

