| 1. **Study population**   The study period will be from 1st April 2007 to 31st December 2015.  We will perform all analyses in patients that were eligible for all linkages and fulfil the following:   1. registered at a participating English practice prior to the transfer of identifiers to the trusted third party for matching for at least a year before their entry into the study 2. their practice is deemed to be contributing ‘up-to-standard' (UTS) data at study start date 3. they had a valid identifier for linkage (NHS number for ONS mortality and HES data, postcode for IMD) 4. they had not opted out or dissented from CPRD or the linkage scheme 5. individual record is of ‘acceptable' research quality as verified by the CPRD.   **Cohort 1**: Individuals who were registered with a GP contributing to CPRD between 1st April 2007 and 31st December 2015 and who have a complete record on age, gender and IMD are eligible for inclusion in this study (see *P. Plans for addressing missing data*). Patients must have been registered with their GP for at least one year before entering the study with the exception of children aged less than one year who will be assumed to be born into the Practice. Patients can enter the study late or leave the study early in order to include patients who died within the study period (who might be inherently less healthy). Patients enter the study population on the latest of the following dates: continuous registration with GP for 12 months or 1st April 2007. Where patients registered with their GP after the 1st April 2007, patients enter the cohort after 12 months of continuous registration. Patients exit the cohort on the earliest of the following dates: the date the patient died, the date the patient left the practice, or 31st December 2015.  Subsequent studies are nested within cohort 1 (see Error: Reference source not found):   1. Nested cross-sectional study: Patients within cohort 1 with at least one prescription of an antibiotic 2. Nested cohort studies of specific infection syndromes: Patients within cohort 1 with at least one GP consultation for a specific infection syndrome (respiratory, urinary, skin/soft tissue). For these cohorts, patients will enter the cohort on the day of the consultation for infection. Patients will leave the cohort on the earlier of: 28 days after initial consultation, death, transfer out of practice or 31st December 2015. Patients can enter and exit the cohort more than once. |

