| 1. **Data/ Statistical Analysis**   *1. Estimate the incidence of i) GP consultations for infection and ii) antibiotic prescriptions*  For every patient in cohort 1, data on all consultations for infection and antibiotic prescriptions occurring within the study period will be extracted. We will estimate the incidence of GP consultations for infection and antibiotic prescriptions. This will be done for all consultations and prescriptions, and then separately for each category of infection and each class of antibiotics, based on chapter 5.1 of the British National Formulary (BNF) (see Appendix Tables 1 & 2). The denominator will be estimated as total person-time contributed by patients in the cohort during the study period. We will use Poisson regression to estimate the adjusted rate of consultation and prescription, taking account of the effect of age, gender, SES, ethnicity, selected co-morbidity, smoking and obesity. Random effects will be included to take account of clustering of observations by practice. Rates will be assessed for overdispersion by additionally fitting a negative binomial model and testing for alpha greater than zero via a likelihood-ratio test. If rates are found to be overdispersed, the negative binomial model will be used instead of a Poisson model. Adjusted rate ratios will be presented with 95%-confidence intervals.  *2. Describe antibiotic prescribing patterns linked to the reason for prescription*  The overall number of antibiotic prescribing episodes will be calculated for each patient individually, counting all recorded prescriptions between 1st April 2007 and 31st December 2015. For each episode, a clinical indication will be ascertained. Read codes for a diagnosis or symptom of infection recorded on the same day as the antibiotic prescription will be assumed to represent an indication for the prescription. Where more than one possible indication within the same type of infection is recorded on the day of prescription, the more granular code will be used. If multiple indications across different types of infection are recorded, the prescription will be labelled as having multiple indications. Conversely, if no infectious indication for a prescription was found, the prescription will be labelled as having no infectious indication and we will look for any non-infectious codes associated with the date of antibiotic prescription. The ten most common indications will be established and compared to the same numbers for the period from 1998-2001.14 This approach will be replicated for each class of antibiotics based on chapter 5.1 of the BNF. Patterns of repeat consultation or prescription during episodes of infection which may be prolonged will be investigated for each antibiotic prescription extracted in objective 1. We will define a new episode as a consultation or prescription recorded at least 28 days after any previous consultation for infection or antibiotic prescription. We will undertake sensitivity analyses to investigate the impact of using different time periods to define an episode. We will also examine the use of regular (prophylactic) antibiotic treatment.  Proportions and appropriate 95%-confidence intervals will be calculated and all results will be stratified by age-group, gender, SES, ethnicity, selected co-morbidity, obesity and smoking status. Descriptive data will be displayed graphically.  *3. Estimate the incidence of adverse outcomes in the following 28 days*  For each of the selected clinical infection syndromes in the nested cohort study, events in CPRD, HES and ONS will be searched for all adverse outcomes of interest (see *M.* Exposures, Health Outcomes§ and Covariates). Crude incidence rates of for each outcome will be calculated for patients who were treated (exposed) and not treated (unexposed) with an antibiotic. The denominator will be estimated as the total person-time contributed by patients at risk of each adverse outcome, taking account of the fact that this will be different for each outcome. For example, exposed and unexposed patients cannot consult General Practice if they have been admitted to hospital and should therefore not contribute to the denominator during this period when estimating rates of GP re-consultation in the 28 days following consultation for infection. A Poisson regression model will be used to estimate adjusted rates of adverse outcomes in each group, controlling for age, gender, socio-economic status, ethnicity, co-morbidity, obesity and smoking status and assessing for interaction between age and co-morbidity. Random effects will be included to take account of clustering of observations by practice. If the outcomes are overdispersed, negative binomial models will be used instead of Poisson models. Adjusted rate ratios will be presented with 95%-confidence intervals.  *4. Estimate the number of patients needed to treat with antibiotics to avoid one infection-related adverse outcome*  For each clinical infection syndrome-related adverse outcome identified in objective 3, the odds of that outcome in the 28 days following consultation for those treated with antibiotics (unexposed) and not treated with antibiotics (exposed) will be estimated using logistic regression. We will calculate adjusted odds ratios for the protective effect of antibiotics, adjusting for age, gender, SES, ethnicity, year/season, co-morbidity and the probability of receiving antibiotic treatment (see *O. Plan for addressing confounding*) and assessing for interactions with age and co-morbidity. We will use mixed models to adjust for clustering at a practice level and to take account of clustering of observations within a patient due to repeat episodes of infection. Where there is a significant effect of antibiotics between treated and untreated patients, the NNT or NNH to prevent one individual from developing an adverse outcome is calculated as *1/(absolute risk difference)*. A significant effect will be defined by a p-value < 0.05 for the coefficients of antibiotic treatment and its interactions. To avoid an arbitrary cut-off point, p-values close to 0.05 will also be assessed but discussed separately. The NNT will then be used to assess the clinical relevance of any significant differences found. Whilst the relative risk reduction (RRR) may be similar, the NNT may be different due to differing background risk. This will be explored.  *5. Develop risk prediction tools to support clinical decision making*  For each cohort (i.e. for each of the clinical syndromes of UTI, RTI and SSTI), we will develop a logistic regression risk model to predict the risk of adverse outcomes if patients are treated versus not treated with antibiotics. Models will be developed on a random sample of 80% of the observations within a cohort, reserving 20% of the data to estimate the model’s predictive performance.  A negative outcome will be defined as the occurrence of any of the following within 28 days following the index consultation: hospital admission for infection or complication; re-consultation for infection; A&E admission; death. Antibiotic treatment will be defined as a prescription of an antibiotic on the day of consultation for clinical syndrome. Risk factors will be selected based on the analyses outlined in objectives 1-4 and broadly grouped into: socio-demographic variables, co-morbidity and clinical presentation. Biologically plausible interactions between risk factors and age and between risk factors and co-morbidities will be examined.  Whereas age and sex will be forced into the model, other risk factors will be added in order of their significance in objective 4. Risk factors will be kept in the model if they improve the predictive performance of the model as defined by model discrimination and model calibration.17 For example, a risk factor will be used in the model if it improves discrimination and/or calibration. If a variable improves discrimination but reduces calibration, it will still be included in the model, but will be omitted if it increases calibration at the cost of discrimination.  Model discrimination, i.e. the model’s ability to correctly identify patients with and without an outcome, will be estimated using the concordance (c) statistic.18 The c statistic represents the probability that between two randomly chosen patients, one with the outcome and one without, the model assigns a higher score to the patient with the outcome. As a second measure, model calibration will be assessed using the Hosmer-Lemeshow test.18 We will additionally assess model calibration graphically for reasons for poor calibration by comparing the mean observed outcome in deciles of predicted risk. In this calibration plot, the intercept indicates the extent to which predictions are systematically too low or too high, while the slope reflects overfitting of the model.  For each model, we will estimate the internal validity of discrimination and calibration estimates using cross-validation with bootstrap subsampling based on 1000 iterations. In a secondary analysis, we will assess model performance in subgroups by age, sex and co-morbidity.  Finally, we will develop a simplified scoring system using the risk factors in the model,17 assigning the total score to a specific absolute risk of adverse outcomes in the 28 days following consultation, comparing outcomes if an individual is treated versus not treated with antibiotics. We will assess the predictive performance of the risk scores using the approaches outlined above. |

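### Objective 3 (step 3) allows for clustering by practice only, so confidence intervals for patient-level rate ratios ignore repeat episodes of the same patient, which step 4 does model

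*Protocol*

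**What the plan says.** Section K (Study population) starts each entry to a syndrome cohort at a consultation and ends it at the earliest of "28 days after initial consultation, death, transfer out of practice or 31st December 2015". It adds: "Patients can enter and exit the cohort more than once". No cap or first-episode rule is given.

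Section N, step 3 (Objective 3) states: "A Poisson regression model will be used to estimate adjusted rates of adverse outcomes in each group". Its clustering statement is "Random effects will be included to take account of clustering of observations by practice", its fallback is "If the outcomes are overdispersed, negative binomial models will be used instead of Poisson models", and its output is "Adjusted rate ratios will be presented with 95%-confidence intervals".

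Section N, step 4 (Objective 4) takes the adverse outcomes of step 3 and uses mixed models for practice and also "to take account of clustering of observations within a patient due to repeat episodes of infection".

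Aim 3, the aim that step 3 serves, is a comparison between kinds of patient: "comparing patients with each listed age/co-morbidity group (including smoking status and obesity) to non-comorbid patients".

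**The concern.** The protocol recognises in step 4 that episodes of one patient are correlated, but it leaves this out of step 3 and gives no reason for the difference. The contrasts that Aim 3 names are largely fixed within a patient: co-morbidity, obesity, smoking and age group. For such contrasts a second episode of the same patient brings less new information than a new patient would, and a practice random effect does not capture that. The 95% intervals would then not have their stated coverage. The groups under comparison may also be those with the most repeat episodes. The Rationale reports that more than half of prescriptions go to fewer than 10% of patients, who have high co-morbidity. That concerns prescriptions rather than episodes, so it is only suggestive.

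**Working it through.** The protocol states no design effect, so there is no figure to reproduce. The size can only be shown as a range.

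**Inputs from the protocol.** Outcome risks of 0.04% (rare outcomes) and 2.4% (the planning risk for composite outcomes), both from Section I.

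**Assumed inputs.** Episodes per patient m = 2 to 4, equal across patients. Between-patient variance of the rate multiplier (mean 1) v = 0.25 to 1, after covariate adjustment. Mean events per episode μ of 10% and 20% for common outcomes; the Limitations section names re-consultation as a more common outcome but gives no rate.

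**Case A: events per episode are Poisson counts given the patient.** For a patient-level covariate:

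- Poisson model: true SE / model SE = √(1 + m·μ·v).
- Episode-level negative binomial with α = v: √[(1 + m·μ·v)/(1 + μ·v)].
- Coverage of a nominal 95% interval = 2Φ(1.96/ratio) − 1.

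Worked example at μ = 0.20, m = 4, v = 1: √1.80 = 1.34 under Poisson (coverage 85.6%) and √(1.80/1.20) = 1.22 under the negative binomial (coverage 89.0%).

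| μ | Poisson SE ratio | Coverage | Negative binomial SE ratio |
|---|---|---|---|
| 0.04% | 1.00 | 95.0% | 1.00 |
| 2.4% | 1.01 to 1.05 | 94.9% to 93.9% | 1.00 to 1.03 |
| 10% | 1.02 to 1.18 | 94.4% to 90.2% | 1.01 to 1.13 |
| 20% | 1.05 to 1.34 | 93.8% to 85.6% | 1.02 to 1.22 |

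The negative binomial recovers part of the gap but never all of it. It adds variance to each row and still treats one patient's rows as independent.

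**Simulation check of case A.** There were 60 runs with 40 practices fitted as fixed effects, about 3 episodes per patient and a log-scale patient SD of 0.8. Sixty runs are too few to judge coverage, so only the SE ratios are used.

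- Co-morbidity, μ = 20%: the patient-clustered SE was 1.31 times the Poisson SE and about 1.20 times the negative binomial SE.
- Co-morbidity, μ = 2.4%: 1.035 and 1.024 times.
- Antibiotic treatment, which can vary between a patient's episodes, μ = 20%: 1.09 to 1.21 times the Poisson SE and 1.00 to 1.11 times the negative binomial SE, as the within-patient correlation of prescribing rose from 0 to 0.6.

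**Case B: each row is strictly 0 or 1, with follow-up not stopped at the event.** The row variance is μ(1 − μ), but the Poisson model uses μ. With within-patient correlation ρ the ratio is √[(1 − μ)(1 + (m − 1)ρ)].

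- μ = 20%, m = 3, ρ = 0.05: √(0.80 × 1.10) = 0.94, coverage 96.3%, so the interval is slightly too wide.
- μ = 10%, m = 3, ρ = 0.05: √(0.90 × 1.10) = 0.995, almost no error.
- μ = 20%, m = 6, ρ = 0.10: √(0.80 × 1.50) = 1.10, coverage 92.6%, too narrow.

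Because ρ = μv/(1 − μ) here, the squared ratio is 1 + μ[(m − 1)v − 1]. Intervals are too narrow only when (m − 1)v exceeds 1. On the assumed ranges at μ = 20%, the ratio runs from √0.85 = 0.92 (m = 2, v = 0.25) to √1.40 = 1.18 (m = 4, v = 1). In this case the row variance lies below the mean, so an overdispersion test on episode rows would not be expected to trigger the negative binomial fallback.

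**The case against.** **Objective 3 is descriptive and little depends on it.** Section O says that Objectives 1 to 3 describe rates. The p < 0.05 rule, the NNT and the order in which risk factors enter the Objective 5 model all rest on step 4. This stands and limits the consequence. Step 3 still reports intervals for named group comparisons, and those intervals should have their stated coverage.

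**Section O already covers it.** It mentions random effects for multiple episodes of the same patient. That sentence is about controlling for differences in prescribing habits, in a section that calls confounding relevant only to Objectives 4 and 5. It does not forbid a patient level in step 3, but it does not supply one either.

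**The detail belongs in an analysis plan.** Whether step 3 is fitted on episode rows or on person-time summed per patient is indeed unstated. With one row per patient, a negative binomial would absorb between-patient variation. But treatment can differ between a patient's episodes, and step 3 does not describe such summing. Nor does it leave clustering open: it names practice, and the next step names practice and patient.

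**Stronger readings that the protocol does not support.**

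- A reader might infer that all step 3 intervals are too narrow. Case B shows that the direction can reverse. Death cannot recur, and the treated-versus-untreated contrast is less affected.
- A reader might put generous values into the textbook design effect 1 + (m − 1)ρ. With m = 8 and ρ = 0.20 it is 2.40, which implies standard errors 35% too small and coverage of 79.4%. Neither value is in the protocol, and the formula omits the (1 − μ) factor for 0/1 rows. At the 2.4% planning risk, ρ = 0.20 would need v = 0.20 × 0.976/0.024 = 8.1, and even ρ = 0.05 would need about 2.0, after adjustment for age, co-morbidity, smoking and obesity.
- A reader might extend the point to Objective 1. Step 1 also names practice only, but it uses total person-time per patient and does not set up repeated 28-day episodes.

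**Conclusion.** The point holds as an inconsistency in the variance structure. As written, step 3 ignores within-patient dependence that step 4 models, for the contrasts where it matters most, and the stated fallback does not repair this. On the assumed ranges the consequence is nil at 0.04% risk and trivial at 2.4%. For common outcomes it is material only towards the upper end of the assumptions (m = 4, v = 1: SE ratio 1.18 at 10% and 1.34 at 20% if events are counts). With strict 0/1 rows the error may be smaller, absent or reversed. The conclusion does not rest on a particular size: the step 3 intervals for patient-level factors are mis-specified, and the correction is cheap and already half-written in the protocol.

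**What to change.** Add one sentence to step 3 stating that standard errors are cluster-robust at patient level or higher. Clustering on practice is a convenient choice: it also covers patients within practice, and it corrects the Poisson variance when rows are 0/1. The minimum alternative is the patient-within-practice random effect already stated for step 4, although this alone does not correct the variance for 0/1 rows. It would also help to state whether the row is an episode and whether follow-up for an outcome stops at its first event.

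The cost is more computing time and, for common outcomes, usually somewhat wider intervals. No new data are needed.

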| 1. **Exposures, Health Outcomes§ and Covariates**   **§***Please note:**Summary information on health outcomes (as included on the ISAC application form above) will be published on CPRD’s website as part of its transparency policy*  *Exposure*  Exposures will include i) prescription of an antibiotic ii) GP consultation for suspected infection (see Appendices: Table 1 – Codelist for antibiotics, Table 2 – Codelist categorising indications for antibiotic use and Table 3 – Codelists to identify patients with suspected respiratory tract, urinary tract or skin/soft tissue infection)  *Health Outcomes*  The following outcomes (within 28 days of presentation in primary care) will be separately considered for analysis:   - Re-consultation for the same type of infection (CPRD; see Appendix Table 3) - Re-consultation for a side effect of antibiotic treatment (CPRD; see Appendix Table 4a –side effects of antibiotic treatment) - Complications of infection in primary or secondary care (CPRD and inpatient HES; see Appendices: Table 4b and 4c – complications of infection; depending on the indication) - Admission to Accident & Emergency (HES A&E) - All-cause hospitalisation (inpatient HES) - All-cause mortality (CPRD, HES and ONS)   We will undertake a sensitivity analysis to investigate the impact of excluding outcomes that occur on the same day as the exposure. The impact of different time windows will be explored, informed by a literature review on the natural history of the duration of different infections.  *Covariates*  We will include the following covariates:   - Age (classified as 0-4, 5-17, 18-44, 45-64, 65-84, 85-94 and 95+, years of age inclusive) - Sex (female and male) - Index of Multiple Deprivation (IMD; 1-5) - Co-morbidities (coded as indicator variables based on national guidance from Public Health England3 and feasibility1; see Appendix Table 5 for comorbidity code list)   - Diabetes   - Chronic Kidney Disease (CKD)   - Chronic Obstructive Pulmonary Disease (COPD)   - Asthma - Obesity - Smoking status15 - Season (months or quarters) and year - Ethnicity   We will undertake a sensitivity analysis of the impact of coding co-morbidities as binary indicator variable and as total number of co-morbidities. |

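### In the step 2 episode counts, the 28-day rule lets regular (prophylactic) prescriptions open and block episodes of infection, and varying the window length does not cure this

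*Protocol*

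**What the plan says.** All of this stands in step 2 of the Protocol's Data/Statistical Analysis section (section N), unless another place is named.

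- The first count: "The overall number of antibiotic prescribing episodes will be calculated for each patient individually, counting all recorded prescriptions".
- Indications are assigned from Read codes on the day of the prescription. Where there is none, "if no infectious indication for a prescription was found, the prescription will be labelled as having no infectious indication", and non-infectious codes are then sought.
- The purpose of the episode analysis: "Patterns of repeat consultation or prescription during episodes of infection which may be prolonged will be investigated for each antibiotic prescription extracted in objective 1".
- The rule: "We will define a new episode as a consultation or prescription recorded at least 28 days after any previous consultation for infection or antibiotic prescription".
- The planned check on it: "We will undertake sensitivity analyses to investigate the impact of using different time periods to define an episode".
- Regular treatment: "We will also examine the use of regular (prophylactic) antibiotic treatment". No definition is given, and nothing says that such prescriptions leave the episode count.
- Step 2 results are stratified by age group, gender, SES, ethnicity, co-morbidity, obesity and smoking.

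**The concern.** The episode is meant to be an episode of infection, but the rule that builds it uses prescriptions whether or not an infection was recorded. A patient on regular treatment supplies a prescription about once a month. Depending on a day or two in the issue interval, each prescription either starts a new episode or extends a single unbroken one. A real infection in such a patient nearly always falls within 28 days of some prescription, so it starts no episode.

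The error is not a uniform shift. It sits in patients on regular treatment. If their share differs between co-morbidity groups, the stratified episode counts will differ for a reason unrelated to how often those groups have infections or how long the infections last.

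The rule also ignores infection type: a respiratory infection on day 0 and cellulitis on day 14 are one episode. That is a lesser matter, because it is a defensible choice, but its effect grows with infection frequency and no planned analysis would show it.

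**Working it through.** The Protocol gives no count or rate that depends on this rule, so there is no figure to reproduce. The rule is applied as written: an event opens an episode if it falls at least 28 days after the most recent infection consultation or antibiotic prescription of any kind.

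**1. Regular series without infection, 365 days, first issue on day 0.** The number of issues is floor(364/gap) + 1. If the gap is at least 28 days every issue opens an episode; otherwise only the first does.

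| Gap (days) | Issues | Episodes, 28-day rule |
|---|---|---|
| 26 | 15 | 1 |
| 27 | 14 | 1 |
| 28 | 14 | 14 |
| 29 | 13 | 13 |
| 30 | 13 | 13 |
| 31 | 12 | 12 |

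Real intervals vary. With whole-day intervals averaging 28 days and SD 2 (assumed), simulation gives a mean of about 8 episodes a year (5th to 95th percentile 6 to 11).

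**2. Acute infections in the same patients.** Infections are assumed to fall at random, 1 to 3 a year.
- Gap 26 to 28 days: every infection lies less than 28 days after an issue, so none opens an episode.
- Gap 30 days: only the last 2 of every 30 days are open, so at most 2/30 = 6.7% are expected to count. Simulation gave 5% to 7%.
- Gap 31 days: at most 3/31 = 9.7%.
- The repeats themselves still open about 10 to 12 episodes a year. For a 28-day gap, (365/28) × exp(−rate × 28/365) gives 12.1, 11.2 and 10.4 at rates 1, 2 and 3.

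**3. Does varying the window help?**
- Windows of 14 or 21 days count every issue in the table, including the 26- and 27-day series (15 and 14 episodes). They uncover some acute infections but inflate the count further.
- Windows longer than 31 days merge every series in the table into one episode, and then every acute infection in these patients is hidden.
- In patients not on regular treatment, a longer window absorbs more separate infections: 1 − exp(−3 × 28/365) = 21% at 3 a year with 28 days, against 1 − exp(−3 × 42/365) = 29% with 42 days.

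No window length separates regular issues from infections.

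**4. Size in a stratified comparison.** The Protocol does not give the share of patients on regular treatment. At 8 to 14 counted episodes each, every 1 percentage point of patients on year-round treatment (assumed) adds 0.01 × 8 = 0.08 to 0.01 × 14 = 0.14 episodes per person-year if issue is about monthly, and almost none if it is every 26 or 27 days.

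**5. Infection type.** The Sample size considerations section puts urinary cases at 1/5 and skin/soft tissue cases at 2/5 of respiratory cases, a ratio of 5:1:2 for respiratory, urinary and skin. Infections are assumed independent, at total rate λ a year.
- Type-blind count: λ·exp(−28λ/365).
- Type-specific count: the sum over types of λᵢ·exp(−28λᵢ/365), with λᵢ = 5λ/8, λ/8 and 2λ/8.

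| λ | Type-blind | Type-specific | Type-blind lower by |
|---|---|---|---|
| 0.33 | 0.322 | 0.326 | 1% |
| 1 | 0.926 | 0.965 | 4% |
| 3 | 2.383 | 2.696 | 12% |
| 6 | 3.787 | 4.858 | 22% |

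**The case against.** The strongest reply is that the rule has a narrow job. This is right, and it limits the point. Step 1 rates use all consultations and prescriptions, separately by infection category, with no 28-day gap. Indications are attached to each prescription from same-day codes, so cellulitis on day 14 keeps its own label, and an uncoded repeat is labelled as having no infectious indication. The nested cohorts have their own entry and exit rule in the Study population section, and steps 3 to 5 do not cite the episode rule. The label does not settle the matter, however: it marks the prescription but does not stop it from opening an episode or blocking the next one.

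It can also be said that prophylaxis is named for examination and that its detection may be left to a statistical analysis plan. The definition of a regular series could be. But the Protocol itself fixes the counting rule, and that rule makes no exception.

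On infection type the objection largely stands. A type-blind gap prevents one illness, recoded at a second visit, from counting twice, and the Limitations section warns of coding variation between practices. The type-specific count is not the truth against which the other is wrong.

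Three stronger readings are tempting and not supported:
- A reader might see a contradiction with the Exposures, Health Outcomes and Covariates section, which lists "Re-consultation for the same type of infection". That defines an adverse outcome, not a new episode.
- A reader might infer that the study's premise, "more than half of all antibiotic prescriptions in primary care are issued to less than 10% of patients", is undermined. The premise counts prescriptions, which the rule does not touch.
- A reader might treat the two uses of the word episode in step 2 as conflicting definitions. Prescriptions on days 0, 7 and 14 are three by the first count and one by the rule, but the two can be read as different units, so this is mainly terminology.

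**Conclusion.** The point holds for the step 2 episode counts and their stratification, and not beyond them. Under the literal rule, regular issue every 28 to 31 days counts as 12 to 14 new episodes a year, issue every 26 or 27 days counts as one, and at most about one in ten acute infections in these patients opens an episode. The counts of 12 to 14 and of one follow from the rule with fixed intervals; with intervals averaging 28 days and SD 2 the figure is about 8. The share of acute infections counted assumes that they fall at random.

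The overall distortion cannot be stated from the Protocol. Any percentage for the whole population would rest on an assumed prevalence of regular treatment, and a reader should not take one from this point. The infection-type figures (1% to 22%) assume independent infections and show how far two defensible definitions diverge, not an error. The change is worth making because it is cheap and step 2 answers a stated aim, but the antibiotic effect estimates do not depend on it.

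**What to change.** 1. Before counting episodes, identify regular prescription series by a stated operational definition, for example three or more issues of the same antibiotic at regular intervals with no same-day infection code. Report these series separately as regular treatment, and let them neither open nor block an episode of infection.
2. Vary that definition within the sensitivity analyses already planned for the episode window.
3. Keep the type-blind 28-day rule as primary if preferred, and add a sensitivity analysis that defines episodes within infection type. State there how a prescription without an infection code is assigned when no episode, or more than one, is open.
4. Call the first count in step 2 the number of prescriptions, and keep the word episode for the 28-day unit.

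The cost is wording and programming; no new data are needed. The small downside is that a threshold for a regular series must be chosen, and some short runs of treatment for a real infection may be misclassified at its edge. Item 2 shows how much that matters.
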